### Secondary outcomes

#### Quality of sleep

Quality of sleep during the last month will be assessed using the Pittsburgh Sleep Quality Index (PSQI). This index has been translated and validated into Portuguese. It consists of 19 questions grouped under seven domains: subjective sleep quality; sleep latency; sleep duration; usual sleep efficiency; sleep disturbances; use of medications; and diurnal dysfunction. Each domain is scored (0 to 3) and a total score (0 to 21) is calculated as follows: scores ranging from 0 to 4 are indicative of good sleep quality; scores from 5 to 10 suggest poor sleep quality; scores above 10 are suggestive of sleep disorders. Five other questions are answered by participants’ spouses or partners, and further characterize sleep quality [38,39].

#### Anxiety

Anxiety will be assessed using the State*-*Trait Anxiety Inventory (STAI), which has been translated and validated to the Portuguese language. It consists of two independent scales, with 20 questions each, measuring anxiety as a trait (in general) and as a state (at the moment). Each question is scored (from 1 to 4), and scores for the scales range from 20 to 80 as follows: mild anxiety (20 to 34); moderate anxiety (35 to 49); high anxiety (50 to 64); and very high anxiety (65 to 80) [40,41].

#### Stress

Stress will be assessed with the Perceived Stress Scale (PSS-10), which has also been translated and validated [42]. It consists of 10 questions with scores ranging from 0 to 4. Some questions (4, 5, 7 and 8) suggest absence of stress and have an inverted scoring system. Total scores range from 0 to 40, and higher values suggest higher stress levels [43].

#### Depression

The Beck Depression Inventory (BDI) will be used in order to assess depression. This inventory, which has been translated and validated into Portuguese, consists of 21 groups of four statements, assessing depressive symptoms over the last week, such as hopelessness, irritability, guilt, feelings of being punished, as well as physical symptoms such as fatigue, weight loss, decreased libido. Scores below 10 suggest lack or minimal depressive symptoms; from 10 to 18, mild to moderate depression; from 19 to 29, moderate to severe depression; and symptoms of 30 or more are suggestive of severe depression [40].

#### Oral health

Oral health will be assessed using the Oral Health Impact Profile - 14, a shortened version of the Oral Health Impact Profile - 49 [44]. The questionnaire has been translated and validated into Portuguese [45]. It consists of 14 questions with five response options: (0) never; (1) rarely; (2) sometimes; (3) often; and (4) always. Total scores range from 0 to 56, and higher scores are suggestive of poorer oral health [46].

#### Intervention

After the initial assessment, participants will receive information about bruxism, including its symptoms and consequences. They will also be educated about the study procedures. All participants will be submitted to the same assessments, at baseline, immediately after treatment, and at 2-month follow-up.

In that assessment at the 2-month follow-up, participants will receive educational material, with the purpose of providing important information about how to maintain the control of the bruxism after physical therapy interventions or dental treatment [15,16,47].

### Group 1: massage and stretching

The routine to be used in this group (stretching, massage, and diaphragmatic breathing) is described in Table 1[15,35,36,48-51].

**Table 1 T1:** Description of the massage and stretching exercises

**Interventions**	**Description**	**Sets/duration**
Massage	Patient lying supine knees semi-flexed and head on pillow with proper height.	Inspiration/Pause/Expiration: 3:3:3 seconds, five sets
	Diaphragmatic breathing training.	
	**Extra-oral:** sliding, kneading, friction, and trigger points release (ischemic compression) with cream and emphasis on the masseter, anterior temporalis, and muscles of the neck as the upper trapezius and sternocleidomastoid, bilaterally.	Ischemic compression (maximum 60 seconds with 10-second rest between compressions), five sets
	**Intra oral:** sliding, trigger points release (ischemic compression), and circular and transverse friction, with glove, on the masticatory muscles, with emphasis on the masseter, bilaterally.	
Muscle stretching exercises	Patient lying supine knees semi-flexed and head on pillow.	Three sets of 30 seconds
	**Masticatory muscles:** Passive exercises with the help of the therapist (using gloves): elevators of the jaw (masseter, temporalis and medial pterygoid), retrusores (posterior temporal, digastric), lateral (contralateral lateral pterygoid) and circular movements of the jaw.	
		Intervals between sets of 10 seconds
	Patient sitting, feet flat on the ground and spine aligned.	
	**Muscles of the head and cervical spine:** Passive exercises with the help of the therapist: extensor (upper trapezius, levator scapulae, suboccipital), flexor (sternocleidomastoid and anterior scalene), lateral flexor (sternocleidomastoid, upper trapezius, middle and posterior scalenes, bilaterally), and rotators (upper trapezius and sternocleidomastoid contralateral), bilateral.	

### Group 2: relaxation and imagination therapies

The routines to be adopted will focus on progressive muscular relaxation associated to imagination and diaphragmatic breathing. They are described in Table 2[18,52-54].

**Table 2 T2:** Description of the relaxation and imagination therapies

**Interventions**	**Description**	**Sets/duration**
Progressive muscle relaxation	Patient sitting with feet and head supported.	Inspiration/Pause/Expiration: 3:3:3 seconds, five sets
	Diaphragmatic breathing training.	
	First to third session: contraction and relaxation of the muscle groups: arm, forearm and hands; frontal, eyes and nose; mouth and jaw.	
	Fourth to sixth session: contraction and relaxation of the muscle groups: neck; shoulder; mouth and jaw.	
		Contraction/Relaxation: 10:20 seconds, two sets of each muscle group
	Seventh to ninth session: repeating sequence of previous sessions;	
	Tenth to 12th session: complete sequence of the relaxation.	
Imagination	Patient sitting with feet and head supported and closed eyes.	Three scenes (6 to 9 minutes each)
	Patient in relaxation (mostly jaws) and concentration in mental imagery of the scenes of your own, verbally guided by the therapist, with themes such as:	
	- Sunset	
	- Clouds	
	- Rivers	
	- Flowers	
	- Mountains	
	- Forests	
	- Beaches	
	- Other	

### Group 3: dental treatment

Participants in this group will be treated by a dentist, and will be submitted to the same assessments and education. Restoring treatment will involve direct reconstruction of the anterior guides (incisive faces of the incisive and canine teeth) with resin. Two individual sessions will be conducted 1 week apart, and each will last up to 2 hours. Patients will be reassessed 30, 60, and 90 days after treatment end.

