### Study aim

The aim of this study is to compare three treatments: two distinct physical therapy interventions (massage with stretching and relaxation and imagination therapies) with dental treatment in individuals with bruxism. In particular, we aimed to focus on pain, mandibular range of motion, sleep quality, levels of anxiety, stress, and depression, as well as on the overall status of oral health.

The hypothesis of this study is that the individuals with bruxism who receive one of physical therapy interventions (massage and stretching or relaxation and imagination therapies) will have greater reduction in pain intensity levels and better mandibular range of motion, sleep quality, levels of anxiety, stress and depression, and overall status of oral health compared to individuals who receive dental treatment as assessed immediately after the 6-week physical therapy intervention and that these benefits will be maintained until reassessment 2-month follow-up.

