## Methods/Design

This study will be a RCT comparing two physical therapy interventions with dental treatment. Physical therapy will last 40 minutes and will happen twice a week for 6 weeks. Sessions will be conducted by the same physical therapist. Dental treatment will consist of two individual sessions conducted 1 week apart, each of it lasting 2 hours.

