#### Procedures

All participants will be submitted to the same assessments, which will happen at baseline, immediately after treatment and at 2-month follow-up. Assessments will be conducted by a blinded researcher. Demographic and anthropometric data will be collected, as well as bruxism history. Examinations will also look for degree of severity of the temporomandibular disorder [29], bruxism [28,30,31], and pattern of cervical spine curvature [32]. Primary (pain and mandibular range of motion) and secondary (sleep, anxiety, stress, depression, and oral health) outcomes will be assessed.

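### The assessment clock is fixed inconsistently; counted from each arm's own treatment end, both analysed visits fall about 31-35 days earlier in the dental arm

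*Protocol article*

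**What the plan says.** Treatment length differs by arm. Under Methods/Design, "Physical therapy will last 40 minutes and will happen twice a week for 6 weeks", whereas "Dental treatment will consist of two individual sessions conducted 1 week apart, each of it lasting 2 hours".

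Three statements bear on when outcomes are measured:

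- **Common schedule.** Procedures: "All participants will be submitted to the same assessments, which will happen at baseline, immediately after treatment and at 2-month follow-up". The Intervention section repeats it, and Statistical analyses plans an ANOVA across the three groups at those same visits.
- **Group 3 schedule.** The section on dental treatment says that these participants "will be submitted to the same assessments and education", and then: "Patients will be reassessed 30, 60, and 90 days after treatment end".
- **Hypothesis.** Study aim expects more benefit from physical therapy "compared to individuals who receive dental treatment as assessed immediately after the 6-week physical therapy intervention", maintained to the 2-month reassessment.

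**The concern.** The Group 3 list contains no visit at the end of treatment, includes 30- and 90-day visits that the other arms do not have, and meets the common schedule only at about 60 days. The hypothesis points to a third anchor, the end of the physical therapy course. Nothing says which Group 3 visits feed the ANOVA.

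This affects the comparison itself. If every visit is counted from the participant's own treatment end, elapsed time differs systematically between the dental arm and the other two, and an ANOVA at each nominal visit cannot separate that difference from treatment. Participants enter with a pain score of at least 3 (Inclusion criteria), and all receive information about bruxism after the initial assessment (Intervention), so some fall in pain unrelated to the assigned treatment is plausible. Groups 1-2 would have more time for that fall before each analysed visit, which is the direction the hypothesis predicts.

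The sleep outcome has a further problem that needs no assumption about pain: the PSQI asks about the preceding month, which is longer than the whole dental treatment.

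**Working it through.** The plan states no visit days to reproduce. Its one computed figure, 24 per group, is approximately recovered by a two-sided two-sample t-test (difference 2, SD 2, alpha 5%, power 80%): 17 per group, and 17/0.8 = 21.25, rounded up to 22. The present point does not depend on it.

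**1. Visit days.** Day 0 is the first session, and I assume that all arms start equally soon after randomisation, which the article does not state. Twelve sessions, two a week for 6 weeks, end at about day 38-42. Two dental sessions 1 week apart end at day 7. Two months is taken as 56-61 days.

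| Visit, counted from own treatment end | Groups 1-2 | Group 3 | Gap |
|---|---|---|---|
| End of treatment | day 38-42 | day 7 | 31-35 days |
| 2-month follow-up | day 94-103 | day 63-68 | 31-35 days |

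For example, 42 + 60 = 102 against 7 + 60 = 67, a gap of 35 days.

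**2. The Group 3 list.** 7 + 30, 7 + 60 and 7 + 90 give days 37, 67 and 97. Days 37 and 97 lie within about 6 days of the physical therapy visits, but at those visits Group 3 would be 30 and 90 days off treatment, against 0 and about 60 in Groups 1-2. Day 67 matches time off treatment at 2 months but not elapsed time. No pairing matches both clocks.

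**3. PSQI window.** With a 30-day recall and a Group 3 visit on day 7, 30 - 7 = 23 days precede the first dental session, and 23/30 = 77%. At day 38-42 in Groups 1-2 the whole window lies within the treatment period.

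**4. What a time trend could do (assumed, not documented).** A gap of 35 days is 5 weeks. A common fall of 0.1 or 0.2 VAS points a week gives a spurious difference d of 5 x 0.1 = 0.5 or 5 x 0.2 = 1.0 points. Other inputs are SD 2 (Sample size calculation) and 24 x 0.8 = 19.2, so 19 completers per arm. The standard error of a pairwise difference is 2 x sqrt(2/19) = 0.65. The Tukey critical value for three groups and 54 degrees of freedom is |t| = 2.41. Simulating arm means (0, 0, d), the chance of at least one significant physical-therapy-versus-dental pair is:

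| d (VAS points) | d / standard error | False-positive rate |
|---|---|---|
| 0 | 0 | about 4% |
| 0.5 | 0.77 | about 10% |
| 1.0 | 1.54 | about 31% |

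**The case against.** The strongest reply is that a common clock is already implied. The hypothesis places the comparison at a single time, "assessed immediately after the 6-week physical therapy intervention and that these benefits will be maintained until reassessment 2-month follow-up", and if the visits follow that sentence the gap in elapsed time disappears. The dental section also says that Group 3 has the same assessments as the others, so the 30/60/90-day visits may be additional reviews of the restorations. The flow diagram, which is not shown, might settle the matter.

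This limits the point but does not remove it. The article does not establish that the arms will in fact be seen at different elapsed times; it establishes that the anchor is not fixed. The Methods text never carries out the common-week reading, and the dental section does not call its visits extra.

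Two stronger readings are tempting and unsupported:

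- A reader might infer that a Group 3-only schedule would reveal the arm to the blinded assessor. The article does not say who conducts the 30/60/90-day visits, so this does not follow.
- A reader might infer a larger bias from a faster fall in pain. At 0.3 points a week the common fall is 0.3 x 102/7 = 4.4 points by day 102, more than a participant entering at 3 can lose. Regression to the mean also appears largely at the first re-measurement, so a day-7 and a day-42 visit would share much of it. Even 0.2 a week implies 2.9 points by day 102, so the upper end of the range above is already demanding at the second visit.

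Unequal treatment length is a design choice and is not criticised here.

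**Conclusion.** The sections conflict and leave the timing of the analysed outcomes open. Under the plain reading of the Methods, both post-baseline comparisons set the dental arm against arms observed 31-35 days longer. If pain falls over time in all arms, the error favours physical therapy. Most of the dental arm's PSQI window at the first such visit would also predate its treatment.

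The visit arithmetic rests on the stated durations and on equal start times after randomisation. The size of the bias is unknown: the rise from about 4% to about 10-31% illustrates an assumed difference of 0.5 to 1.0 points and does not estimate what this trial will show. Under the common-week reading of Study aim the gap in elapsed time would vanish, so actual confounding is conditional while the inconsistency is certain. Trials status reports that recruitment is under way, and once visits have been collected on arm-specific clocks no analysis can separate arm from elapsed time.

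**What to change.** Reconcile Study aim, Procedures, Intervention, Group 3: dental treatment, and Statistical analyses:

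- Define the two analysed outcome visits from randomisation, identically for all three arms: the end of week 6, which is the anchor in the hypothesis, and 2 months later (about week 14).
- State whether the 30/60/90-day Group 3 visits are separate reviews that do not enter the analysis. They need not be deleted.

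No treatment schedule and no sample size changes. The cost is wording and rebooking. If the 30- and 90-day visits are meant to serve as the outcome visits, they move only from about days 37 and 97 to about days 42 and 102.

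The price is unequal time off treatment: Group 3 would be assessed about 42 - 7 = 35 and 102 - 7 = 95 days after its own treatment end, against 0 and about 60 days in Groups 1-2. A fading dental effect could then look smaller. This should be stated when the results are interpreted.

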### Sample size calculation

Sample size was defined in order to detect a 2-point difference between groups on the pain intensity outcome measured by the Visual Analogical Scales*,* assuming a standard deviation of 2 points. Power was defined as 80% for an alpha of 5% and attrition (drop-outs) of 20%. Accordingly, 24 participants per group will be needed.

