#### Statistical analyses

Descriptive statistics will be used, and data will be summarized using mean, standard deviations, and percentiles. Normality of data distribution will be tested using the Kolmogorov-Smirnov test. Normal variables and comparison among three groups (massage with stretching, relaxation and imagination therapies, and dental treatment) will be assessed at baseline, immediately after treatment and at 2-month follow-up using Analysis of Variance. Post-hoc tests will consist of the Turkey test for parametric variables, and the Dunn’s test for non-parametric variables. Analyses will be conducted using SPSS 19 and SigmaStat 3.5. A level of significance of 5% will be used.

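### Outcome visits are tied to the end of treatment, so a patient who stops the 12-session course early has no clearly defined assessment date, and the per-visit ANOVA uses none of that patient's other data

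*Protocol article*

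**What the plan says.** - **Visits.** Procedures gives all participants the same assessments, "which will happen at baseline, immediately after treatment and at 2-month follow-up", and the Intervention section repeats this. Study aim places the first efficacy comparison directly after the 6-week physical therapy course.
- **Treatment.** Methods/Design: "Physical therapy will last 40 minutes and will happen twice a week for 6 weeks", which is 12 sessions. Dental treatment is two sessions a week apart.
- **Losses.** Sample size calculation: "Power was defined as 80% for an alpha of 5% and attrition (drop-outs) of 20" per cent. One rate covers all groups, and the term is not defined as stopping treatment or as loss to assessment.
- **Analysis.** Statistical analyses: the three groups "will be assessed at baseline, immediately after treatment and at 2-month follow-up using Analysis of Variance", with Tukey or Dunn post-hoc tests.
- **Status.** Trials status says that recruitment is under way.

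**The concern.** The visit is tied to an event whose date depends on adherence. Someone who stops after session 4 of 12, at two sessions a week, has stopped at about week 2. The end-of-treatment visit could then fall at about week 2, at the planned week 6, or not at all. Procedures says who is assessed but not when this patient is seen.

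This is a data-collection rule, so it matters before any analysis choice. No later analysis can restore a score that nobody collected, and a score taken at week 2 measures something different from one taken at week 6.

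The stated analysis adds to the exposure. An ANOVA at one visit drops every patient without a value at that visit, and it makes no use of the baseline or other visits of those it keeps. If patients who do worse leave the 12-session arms more often than the 2-session arm, the comparison shifts towards physical therapy, which is the direction of the trial's hypothesis.

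**Working it through.** **1. The plan's own figure.** Inputs from Sample size calculation: "detect a 2-point difference between groups on the pain intensity outcome", "assuming a standard deviation of 2 points", 80% power, alpha 5% (two-sided assumed), 20% drop-outs.
- Normal approximation: n = 2 × (2/2)² × (1.96 + 0.84)² = 15.7, so 16 per group; 16/0.8 = 20.
- Exact t-test: 17 per group; 17/0.8 = 21.25, so 22.
- Alpha halved for two comparisons with dental treatment (normal approximation): 20 per group; 20/0.8 = 25, or 20 × 1.2 = 24.

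The plan says "24 participants per group will be needed". The t-test route comes within 2 of this and the halved-alpha route meets it, so the arithmetic is not in dispute.

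**2. Patients affected.** 24 × 0.8 = 19.2 with data per group. 72 × 0.2 = 14.4, so about 14 patients without data if every drop-out lacks an outcome. That is an upper bound on those a visit rule could recover.

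**3. Possible bias.** Assumptions: SD 2, no true difference, leaving correlated r = 0.3 to 0.7 with a worse score. Both loss patterns average 20%: (25 + 25 + 10)/3 and (30 + 30 + 0)/3.
- Shift in the mean of those remaining in an arm with loss p: r × SD × φ(z)/(1 − p), where z is the normal quantile at 1 − p. Example: p = 0.25, r = 0.3 gives 0.3 × 2 × 0.3178/0.75 = 0.254.
- SE = 2 × √(1/n₁ + 1/n₂), with n = 24 × (1 − p): 18 and 21.6 patients give 0.638; 16.8 and 24 give 0.636.
- The Tukey pairwise rate uses the studentized-range critical value divided by √2 (2.41) and the noncentral t.

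| Loss, physical therapy / dental | r | Bias (points) | Bias/SE | Tukey pairwise false-positive rate |
|---|---|---|---|---|
| 25% / 10% | 0.3 | 0.254 − 0.117 = 0.14 | 0.2 | 2.2% |
| 25% / 10% | 0.7 | 0.593 − 0.273 = 0.32 | 0.5 | 3.5% |
| 30% / 0% | 0.3 | 0.298 − 0 = 0.30 | 0.5 | 3.3% |
| 30% / 0% | 0.7 | 0.695 − 0 = 0.70 | 1.1 | 10.2% |
| equal, same mechanism | any | 0 | 0 | 1.9% |

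The last row is the reference: with three groups, a single Tukey pair has a null rate of about 2%, not 5%. By simulation, the chance of any false pair is about 5% to 8% for the 25%/10% pattern and 7% to 20% for 30%/0%, against a nominal 5%.

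Cross-check with a simpler model: 20% lost in a physical therapy arm, none in dental, and those lost 1, 2 or 3 points worse than those who remain. Bias = 0.2 × gap = 0.2, 0.4 or 0.6 points.

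**4. Power for one Tukey pair.** Noncentrality = d/(2 × √(2/n)).
- n = 19, d = 2: 3.08, power 75%.
- n = 24, d = 2: 3.46, power 85%.
- n = 24, d = 1.8: 3.12, power 76%.
- n = 24, d = 1.6: 2.77, power 65%.

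Full retention gains at most 10 points of power. Dilution to 1.8 uses up nearly all of that, and dilution to 1.6 more than all.

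**The case against.** A reader might infer that patients who stop have no usable endpoint and that the arms will be compared among those who stay. The article says neither. Procedures promises the same assessments to all participants, nothing limits them to completers, and inflating n for attrition is ordinary practice that defines no analysis set. A date can also be derived: Study aim and Methods/Design together imply a planned course end at 6 weeks. This part of the objection stands. What remains is that the text does not say the planned date governs when a patient stops early.

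A reader might also take the 20% as patients who stop treatment but could still be seen. Drop-outs may mean loss to follow-up, and a visit rule would not recover those patients.

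The direction of bias is not established either. The article gives no loss by arm, and patients who improve may also stop early. A false-positive rate of 8% to 19% for the 30%/0% pattern comes from an unadjusted 1.96 threshold; the planned Tukey test gives about 3% to 10%.

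Finally, analysis sets, missing-data rules and sensitivity analyses are commonly left to the full protocol or SAP, which are not shown, so their absence is no finding. That does not cover the two things the article itself fixes: visits tied to treatment end, and an ANOVA at each visit.

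**Conclusion.** The point holds as a weakness in two stated choices. It does not show that outcomes will go uncollected or that the result will be biased. Tying visits to treatment end leaves the date unclear for patients who stop a 12-session course early, and a per-visit ANOVA discards the baseline and other visits that would limit the damage.

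Under the assumed unequal losses the bias is about 0.14 to 0.70 points, or 7% to 35% of the 2-point target, with a Tukey pairwise false-positive rate of about 2% to 10% against a reference of about 2%. Size and direction rest on arm-specific loss and on the link between leaving and outcome, neither of which the document gives. The case for change rests on protection against selective loss and on the precision gained from using baseline. The power gain from retention alone is uncertain.

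**What to change.** **Procedures.** State that stopping treatment is not leaving the study, and that every randomised patient is assessed at the planned end of the allocated course and 2 months after that date, whatever number of sessions was attended. Give the planned date for each arm, counted from randomisation or from the scheduled first session.

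**Statistical analyses.** Replace the separate per-visit ANOVAs with a repeated-measures mixed model on all randomised patients in their allocated group, using baseline and every observed visit. The model reduces exposure to loss that earlier scores predict. It does not remove bias from loss that depends on scores never observed, so the visit rule comes first.

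**Cost.** Wording in two sections and reminder calls to patients who stop sessions, with no extra patients or procedures. The estimated effect may be slightly diluted by non-completers. Because recruitment is under way, the visit rule should be settled promptly.

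### The 80% power statement makes no allowance for the planned Tukey comparisons: after 20% attrition, one pair differing by 2 points has about 75% power

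*Protocol article*

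**What the plan says.** Under Sample size calculation, the protocol article states the target and its assumptions: "Sample size was defined in order to detect a 2-point difference between groups on the pain intensity outcome", "assuming a standard deviation of 2 points". It then gives the operating characteristics and the result: "Power was defined as 80% for an alpha of 5% and attrition (drop-outs) of 20%. Accordingly, 24 participants per group will be needed". No test is named, no adjustment for multiple comparisons is mentioned, and nothing says which pair of groups, or which pattern of three means, the 2 points describe.

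Under Statistical analyses, the three groups are compared at each assessment by analysis of variance. For pairwise follow-up, "Post-hoc tests will consist of the Turkey test for parametric variables" (Tukey is meant). The general level is given as "A level of significance of 5% will be used", with no statement on sidedness.

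The Study aim section hypothesises that patients given either of the two physical therapies will do better than those given dental treatment.

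**The concern.** The hypothesis is about pairs: each physical therapy against dental treatment. A significant overall F test does not show which groups differ, so under the written plan the answer comes from the Tukey test. Tukey holds the familywise error at 5% across all three pairs and so uses a larger critical value than an unadjusted comparison. The sample size statement shows no sign of allowing for this.

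If the allowance is missing, the stated power belongs to a test that the trial will not run. A non-significant Tukey pair would then be read as coming from a trial with a 20% chance of missing a true 2-point effect, when the chance is nearer 25%.

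**Working it through.** **Inputs.** From Sample size calculation: difference 2, SD 2 (standardised difference 2/2 = 1), alpha 5%, power 80%, attrition 20%, 24 per group. From Statistical analyses: three-group analysis of variance, then Tukey. Assumed: two-sided testing, equal attrition in the three groups, normal data with a common SD, no baseline adjustment.

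**Evaluable patients.** 24 × (1 − 0.20) = 19.2, so 19 per group.

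**The plan's own figure, read as a simple two-group comparison.**
- Normal approximation: n = 2(1.960 + 0.842)² / 1² = 15.7, so 16 per group; 16/0.8 = 20 randomised.
- Exact two-sample t-test: 16 per group gives 78.1% and 17 gives 80.7%, so 17 are needed; 17/0.8 = 21.25, so 22 randomised.
- The stated 24 is above both figures. With 19 evaluable, the noncentrality is √(19/2) = 3.082 on 36 df, and power is 85.1%.

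So 24 is sufficient, and slightly generous, for an unadjusted pair.

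**The planned pairwise test (Tukey).** The critical value is q(0.95; 3 groups, 3n − 3 df)/√2. Power comes from the noncentral t distribution with 3n − 3 df and noncentrality √(n/2). At n = 19 there are 54 df, the critical value is 2.410 and the noncentrality is 3.082.

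| Evaluable per group | Power, one Tukey pair, difference 2, SD 2 |
|---|---|
| 19 | 74.7% |
| 20 | 77.3% |
| 21 | 79.6% |
| 22 | 81.7% |
| 24 (no dropout) | 85.4% |

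A simulation of 200,000 runs at 19 per group gave 74.6%. If a significant F test is also required before the pairwise test, the simulated figure is 74.3% when the third group equals one of the pair, and 73.4% when it lies midway.

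Reaching 80% for one Tukey pair takes 22 evaluable; 22/0.8 = 27.5, so 28 per group, or 84 in total.

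**The overall F test at 19 per group (2 and 54 df).** The noncentrality is n × Σ(mean − grand mean)² / SD².
- Means 0, 1, 2 (least favourable for a maximum difference of 2): 19 × 2/4 = 9.5; power 77.0%.
- Means 0, 0, 2 (two groups equal, third differs by 2): 19 × 2.667/4 = 12.67; power 88.2%.

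**Both physical therapies against dental treatment.** If both truly differ from dental by 2 points, simulated Tukey power at 19 per group is 87.4% to show at least one difference and 61.9% to show both.

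**The case against.** The strongest reply is that the sample size section never ties its 80% to a Tukey-adjusted pair. On its stated inputs an ordinary two-sided 5% comparison needs 22 per group with attrition, and 24 gives 85% after attrition. Sizing a trial on an unadjusted pair and then using a corrected post-hoc test is common. The main planned test is the analysis of variance, which exceeds 80% if two groups are alike and the third differs by 2 points. Tukey power to separate at least one physical therapy from dental treatment is 87% if both differ by 2 points. The 75% also assumes the full 20% loss in every group; with no loss the same pair has 85%.

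All of this is numerically right, and it limits the point. A reader might infer that the stated power is simply not delivered, or that the sample size contains an arithmetic error. The documents do not support either reading, because no test is named and the figure is adequate for an unadjusted comparison. A reader might also suspect that 24 came from multiplying 20 by 1.2 when dividing 20 by 0.8 would give 25. The article states neither an evaluable number of 20 nor its method of inflation, so that is conjecture.

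The mismatch remains. The unadjusted t-test that makes 80% true appears nowhere in the analysis section. Attrition of 20% is the plan's own assumption, so 19 is the number at which to judge power. The F test clears 80% only under a favourable pattern of means, and the article does not specify a pattern. Nor is this a detail left to a fuller document: both sections are in the article, and they do not fit each other as written.

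**Conclusion.** The point holds in limited form. The 80% does not allow for the multiplicity-adjusted pairwise tests that the article plans. With 19 evaluable per group, one Tukey pair differing by 2 points has about 75% power (73% to 75% if a significant F test must come first). The shortfall is about 5 percentage points, and the type II risk is about 25% where 20% is implied. The F test lies between 77% and 88% depending on the third mean; the unplanned unadjusted t-test has 85%.

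These figures rest on the assumptions listed with the inputs. The shortfall is modest. It calls for an accurate power statement and does not by itself call for a larger trial.

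**What to change.** Keep 72 patients, name the test to which the power refers, and restate the figure. Suggested wording: *With 24 randomised per group and 19 evaluable after 20% attrition, the trial has about 75% power to detect a 2-point difference (SD 2) in a Tukey-adjusted two-sided pairwise comparison.*

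If the analysis is changed, state the power for the new analysis instead. Limiting the comparisons to each physical therapy against dental treatment with Dunnett's test gives about 79% at 19 per group. Adjusting for baseline pain, with an assumed baseline-to-follow-up correlation of 0.5, reduces the SD to 2 × √(1 − 0.25) = 1.73 and gives about 87% even with Tukey. The article does not give this correlation, so it would need support.

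The cost is one sentence and a slightly less favourable stated power. No extra patients are needed.
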